#### 11.5.1.1 Analysis of Demographics and Other Baseline Characteristics

Demographic characteristics (age, race etc.) will be tabulated by vaccine group on the ITT data set. Quantitative demographic variable age will be described as number of subjects, mean, SEM, minimum, median, maximum, and range. Qualitative demographic variables will be described by number of subjects and percentage by each vaccine group. Group comparisons will be performed to confirm whether the vaccine groups are similar with regard to demographic characteristics. Clinical laboratory results will be tabulated by vaccine group using both quantitative (raw values) and qualitative parameters (relative positions regarding normal ranges in use in the laboratory). The investigator will check the biological parameters (haematology and serum chemistry) and the vital signs. The clinically significant abnormalities will be described. Concomitant diseases at the first visit will be tabulated by vaccine group using the latest version of MedDRA Adverse Event Dictionary.

#### 11.5.1.2 Analysis of Reactogenicity

The primary analysis objectives are to assess the reactogenicity of vaccine administration. Primary analyses will evaluate immediate reactogenicity (every 30 minutes up to 3 hours post-vaccination) and delayed reactogenicity (from Day 0 and Day 14 based on solicited adverse events defined in section 7.2.2).

Binomial proportion for local, systemic reactions and solicited AEs will be calculated along with 95% confidence interval by vaccine group.

#### 11.5.1.3 Analysis of Overall Safety

The safety analysis will include all randomised subjects who have received at least one dose of either of the assigned study vaccines. The overall percentage of subjects with at least one reported adverse event / serious adverse event, with date of onset up to 28 days after vaccination will be tabulated with 95% confidence intervals, by type of adverse event; by severity; and by causality. These events will be summarised and classified by System Organ Class and preferred term MedDRA. They will be displayed by vaccine group as both frequencies and percentages on the ITT data set. All reported adverse events that start post-vaccination would be tabulated. If a given disease is already reported as ongoing at the first visit on the medical history pages, it will be counted and tabulated as a vaccine emergent adverse event only if it worsens after the vaccination with the study vaccines. For each vaccine group vital sign parameters will be summarised visit wise as number of subjects, mean, SEM, median minimum, maximum and range. The changes in vital

*Information contained in this publication is the property of EVI and ICGEB and is confidential and will not be disclosed to third parties without written authorization from EVI and ICGEB. No part of this document may be reproduced, stored in a retrieval system or transmitted in any form or by any means -electronic, mechanical, recording or otherwise - without the prior authorization of EVI and ICGEB*

[figure not shown][figure not shown]

signs for every 30 minutes till 3 hours post-vaccination from pre-vaccination will be calculated and tabulated for each vaccine group.

The investigator will check the biological parameters (haematology and serum chemistry). Newly occurring or worsening lab abnormalities will be assessed and reported by the investigator as adverse events as applicable. Clinical laboratory results will be tabulated by vaccine group at each time point as both quantitative parameters (raw values) and qualitative parameters (relative positions regarding normal ranges in use in the laboratory). Serious adverse events and discontinuation due to adverse event(s) will be described in detail by vaccine group.

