**Vaccination Schedule:**

All subjects will receive three (3) doses of the assigned investigational vaccine or control vaccine on Days 0, 28 and 180 by intramuscular route. Follow-up duration is 365 days/ one (1) year after the first administration of the vaccine.

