### 4.3 Planned Duration of Study Participation/Study Period

The total duration of each subject's participation (excluding allowed window periods) will be approximately 386 which include:

- Pre-screening period of 7 days
- Screening period of 14 days
- Vaccination period of 180 days (refer window period by visit)
- Follow-up period till 365 days (1 year) after the first vaccination (window period of +/- 7 days)

The approximately, total study duration (476 days) includes enrolment period (90 days) and duration of participation of individual subjects (386 days).

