## 4.6 Definition of Study Endpoints

### 4.6.1 Primary Endpoint(s)

The safety profile will be assessed on the basis of the following criteria

- Immediate reactogenicity (any event occurring within the first three (3) hours recorded every 30 minutes after each vaccination, with emphasis on allergic reactions)
- Local and systemic reactogenicity (solicited adverse events occurring from three (3) hours post-vaccination on Day 0 till Day 14 after each dose)
- Any unsolicited adverse events 28 days after each vaccination
- Any Serious Adverse Event (SAE) occurring from the first dose of vaccine till the last follow-up visit.
- Biological safety, 28 days after each vaccination, in reference with the baseline before the first dose, by measuring the following parameters:

- Haematology: RBC count, Haemoglobin\*, Haematocrit/Packed Cell Volume (PCV), MCV (Mean Corpuscular Volume), MCH (Mean Corpuscular Haemoglobin), MCHC (Mean Corpuscular Haemoglobin Concentration), Platelet Count and Total Leukocyte Count (TLC) along with Differential Leukocyte Count (DLC) on Days -14, 28, 56, 180, 208, 365.

\*If the haemoglobin drops below 13 gm/dL, then a direct Coomb's test and a peripheral blood smear/film will be prepared and examined for evidence of possible haemolysis.

- Serum Chemistry: Potassium, Sodium, AST, ALT, Direct, Indirect and Total Bilirubin, Alkaline Phosphatase, Gamma Glutamyl Transpeptidase ( $\gamma$ GT), Creatinine, and Random blood glucose on Days -14, 28, 56, 180, 208, 365.

The Investigator will be responsible for causality assessment i.e. assessment of the relationship of the AE to the assigned study vaccines, using the following definitions: related or not related.

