### 8.4.2 Reporting of Adverse Events

To ensure subject safety, every AE, regardless of suspected causality, occurring after the subject has received the first dose of the vaccine till 28 days after the subject has received each dose of the vaccine will be reported. Information about all adverse events, whether volunteered by the subject, discovered by investigator questioning, or detected through physical examination, laboratory test or other means, will be collected and recorded on the Adverse Event Case Report Form and followed as appropriate. Thus, AEs will be collected through both solicited and unsolicited means and subsequently coded in tabular form using the latest version of MedDRA Adverse Event Dictionary. The subjects will be encouraged to report signs, symptoms, and any changes in health to the Investigator. Severity of each AE will be determined by the staff based on observation and questioning of the subjects. The Investigator will judge the relationship of the event to the study treatments.

Adverse events occurring before the subject has signed the informed consent as well as those which occur in the screening period are recorded on the Medical History. Abnormal laboratory values or test results constitute adverse events if they are not a part of any specific diagnosis, induce clinical signs or symptoms, require any action to be taken or any intervention to be made, and are considered as clinically significant. Such clinically significant abnormal lab values will be recorded on the Adverse Events Case Report Form under the signs, symptoms or diagnosis associated with them and will be followed till resolution or stabilization of the same.

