### 8.5.2 Reporting Serious Adverse Events

To ensure subject safety, every SAE, regardless of suspected causality, occurring after the subject has received the first dose of the vaccine till Day 365 (end of study) must be reported by the Principal Investigator/designee to the Sponsor and DLS within 24 hours of the knowledge of its occurrence. Recurrent episodes, complications, or progression of the initial SAE must be reported as follow-up to the original episode, regardless of when the event occurs. This report must be submitted within 24 hours of the investigator receiving the follow-up information. An SAE that is considered completely unrelated to a previously reported one should be reported separately as a new event.

Every SAE will be reported to the Medical and Safety Monitor at DLS as well as the Sponsor Representatives (both ICGEB and EVI) by telephone/e-mail within 24 hours from observation, regardless of the treatment group or suspected relationship to study vaccines. In addition, for each SAE, the investigator must assess the relationship to the study vaccine, complete the SAE Report Form and send the completed, signed form by e-mail/fax as soon as possible. The telephone and fax number of the Medical and Safety Monitor at DLS will be listed in the investigator folder provided to the study site. The original copy of the SAE Report Form and the fax confirmation sheet must be kept with the case report form documentation at the study site. The initial report should be followed by a full written summary (using SAE Report Form) detailing relevant aspects of the AE, in sufficient detail to allow for a complete medical assessment of the case and independent determination of possible causality. In general, this information includes copies of relevant hospital case records, autopsy reports and other documents where applicable. The initial and follow-up reports shall identify the trial subjects by the unique randomisation number assigned to each subject.

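### The SAE percentage with 95% CI planned in 11.5.1.3 stops 28 days after vaccination, whereas the primary SAE endpoint runs from first dose to the last follow-up visit

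*Supplement*

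**What the plan says.** Section 4.6.1 gives the two kinds of event different windows. Unsolicited AEs are counted for 28 days after each vaccination. The SAE endpoint is "Any Serious Adverse Event (SAE) occurring from the first dose of vaccine till the last follow-up visit". The synopsis repeats both.

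Collection follows the same split. Section 8.4.2 has AEs reported from the first dose and "till 28 days after the subject has received each dose of the vaccine will be reported". Section 8.5.2 separately requires that every SAE "occurring after the subject has received the first dose of the vaccine till Day 365 (end of study) must be reported".

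The analysis does not keep the split. Section 11.5.1.3 plans the overall percentage of subjects with at least one "adverse event / serious adverse event, with date of onset up to 28 days after vaccination will be tabulated with 95% confidence intervals", broken down by type, severity and causality. A single onset limit is attached to both kinds of event.

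The same section also contains two sentences with no such limit. One reads "All reported adverse events that start post-vaccination would be tabulated". The other promises a detailed description, by vaccine group, of SAEs and of discontinuations due to AEs. Section 11.5.1 adds a general rule that categorical variables are summarised with frequencies, percentages and 95% intervals. It names neither SAEs nor a time window.

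**The concern.** A 28-day window suits non-serious unsolicited AEs, because that is how long they are collected. It does not suit SAEs, whose endpoint and collection both run to the end of the study. By joining the two with a slash, 11.5.1.3 carries the AE window over to the SAEs.

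Someone programming the SAE table from that sentence would leave out any SAE starting between Day 56 and Day 180, or after Day 208. The resulting percentage and interval would describe a different quantity from the primary endpoint. In a first-in-human trial whose primary objective is safety, with 10 subjects per dosage arm, a single event decides whether that row reads zero.

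**Working it through.** The plan states no figure for the share of follow-up covered, so there is none to reproduce.

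**Inputs**
- Doses: "All subjects will receive three (3) doses of the assigned investigational vaccine or control vaccine on Days 0, 28 and 180 by intramuscular route" (synopsis, vaccination schedule).
- Follow-up: "Follow-up duration is 365 days/ one (1) year after the first administration of the vaccine" (same place). Section 4.3 allows 7 days either side of the Day 365 visit.
- Onset limit: 28 days after vaccination (11.5.1.3), read here as after each dose.
- Group sizes: 10 subjects per dosage arm, 30 on the investigational vaccine overall (5.3).

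**Share of follow-up covered**
- Windows: Days 0–28, 28–56 and 180–208. They meet but do not overlap, so covered time = 3 × 28 = 84 days.
- Gaps: 180 − 56 = 124 days and 365 − 208 = 157 days, together 281 days.
- 84/365 = 23.0% covered; 281/365 = 77.0% not covered.

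**Sensitivity of the 77%**
- Counting both end days: 86 of 366 days covered, 76.5% not covered.
- Last visit anywhere from Day 358 to Day 372, under either counting rule: 76.0% to 77.4% not covered.
- If vaccination meant the first dose only: 1 − 28/365 = 92.3% not covered.

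**Effect of one SAE at Day 120**

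Clopper–Pearson limits. For 0/n the upper limit is 1 − 0.025^(1/n). For 1/n the lower limit is 1 − 0.975^(1/n), and the upper limit is the 97.5% point of a Beta(2, n − 1) distribution.

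| Group | 28-day rule | Endpoint in 4.6.1 |
|---|---|---|
| One dosage arm, n = 10 | 0/10: 0 to 30.8% | 1/10: 0.3 to 44.5% |
| Pooled investigational vaccine, n = 30 | 0/30: 0 to 11.6% | 1/30: 0.1 to 17.2% |

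**Illustration of dilution**

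Assume a constant SAE hazard over the year, which the documents do not state. A one-year risk p then appears in the 28-day windows as 1 − (1 − p)^(84/365). For p = 5%, 10% and 20% this gives 1.2%, 2.4% and 5.0%. If SAEs cluster soon after dosing, the loss is smaller.

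**The case against.** The strongest reply is that the late SAEs are covered elsewhere. Section 11.5.1 gives categorical variables a percentage and a 95% interval, and having at least one SAE from first dose to last visit is such a variable. Section 11.5.1.3 also says that all AEs starting after vaccination would be tabulated, and an SAE is an AE. SAEs are further to be described by group without any time limit.

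Much of this stands. A reader might infer from the 28-day sentence that later SAEs drop out of the tables and survive only as narratives. The documents do not support that: the unrestricted tabulation sentence arguably includes them. Nor is this the only percentage in the plan with an interval, since 11.5.1 and 11.5.1.2 provide others. Section 8.4.2 is no evidence of truncated SAE data either, because 8.5.2 handles SAE reporting separately and to Day 365.

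The reply does not remove the mismatch. The general rule in 11.5.1 names no SAE window, so the specific sentence in 11.5.1.3 would ordinarily govern the SAE table. The tabulation sentence states no percentage or interval and, read broadly, conflicts with the 28-day limit in its own section.

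A second reply is that Section 11 is an outline and a separate SAP, not among the documents, will hold the details. That would answer a charge of missing detail. Here the protocol states a rule that disagrees with its own endpoint: an SAP that follows the rule repeats the disagreement, and one that departs from it contradicts the protocol text. The phrase may be a drafting slip, but it still needs correcting.

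Finally, the practical effect is limited. The trial is descriptive with 45 subjects, dose escalation rests on Day 14 data after the first dose, and the intervals in the example overlap heavily. This bears on the weight of the point, not on whether it is right.

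**Conclusion.** The point holds within a narrow scope. The only sentence that specifically plans an SAE percentage with a 95% interval restricts it to 84 of 365 days (23% of follow-up time), while the primary endpoint covers the whole period. The defect lies in that percentage and its interval, not in the collection or description of SAEs.

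It would be tempting to say that 77% of SAEs would be missed. The documents do not support this. The figure is a share of time, they give no SAE rate or timing, and vaccine-related events may fall mostly within the windows. They also single out no SAE percentage as the main safety result.

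The 77% assumes that the 28 days run after each dose, that doses fall on schedule and that a subject is followed to Day 365. It stays between 76.0% and 77.4% across the counting rules and last-visit windows tried. The change should be made, because the rule concerns a primary endpoint and correcting it is cheap.

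**What to change.** In 11.5.1.3, separate the two kinds of event:

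- Keep the 28-day onset window for non-serious unsolicited AEs.
- State that the number and percentage of subjects with at least one SAE from first dose to the last follow-up visit (Day 365), with exact 95% CI, will be tabulated by vaccine group.
- Show the percentage with an SAE within 28 days of a vaccination only as a labelled subset of that row.
- Carry the same wording into the SAP.

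The cost is one sentence and one table row. SAEs are already collected to Day 365, so no visit, form or procedure changes.

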10E3/ $\mu$ L, platelet count 150 to 500  $\times$  10E3/ $\mu$ L, Neutrophils 40 to 75 % or Eosinophils > 10 %, Sodium 136 to 145 mEq/L, Potassium 3.5 to 5.1 mEq/L, Random Blood Glucose 45 to 130 mg/dl and Alkaline Phosphatase 40 to 129 U/L (Appendix B and B-1).

11. Subjects with other clinically significant abnormal laboratory values based on the normal reference range (Refer Appendix B and B1) apart from the laboratory parameters listed above.
12. Subject with positive HIV, HBV or HCV test
13. Subject with positive direct Coomb's test
14. Subject with a peripheral blood film/smear with features of haemolysis or any other haematological disorder
15. Subject unable to give written informed consent
16. Subject unable to be closely followed for social, geographic or psychological reasons
17. Subject with previous history of drug or alcohol abuse interfering with normal social function during a period of one year prior to enrolment in the study or positive urine drug test
18. Subject with an abnormal 12-lead ECG at screening associated with relevant clinical symptoms/signs suggestive of cardiac pathology (including conduction disturbances)
19. Subject with an abnormal Chest X-Ray associated with relevant clinical symptoms/signs of respiratory pathology at screening/ anytime in the past 6 months
20. Subject with known history of congenital/hereditary immunodeficiency disorders
21. Subject with acute or chronic pulmonary, reticulo-endothelial, cardiovascular, hepatic, renal or neurological condition, or any other clinical findings that in the opinion of the clinical investigator, may increase the risk of participating in the study
22. Subject with any other condition that in the opinion of the clinical investigator would jeopardise the safety or rights of a participant in the trial or would render the participant unable to comply with the protocol

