### 11.1 Study Conduct Considerations

#### 11.1.1 Sample Size

Since this is a proof of safety and immunogenicity study, true sample size calculations have not been performed and the sample size is approximately 45 healthy male subjects. Therefore no statistical hypothesis will be formulated for this study and only descriptive statistics will be provided for all parameters. The data will be described between vaccines, and within vaccines using the different strata.

A sufficient number of subjects will be screened to enrol a total number of 45 subjects in the study.

- 30 subjects will receive the investigational vaccine (i.e. JAIVAC-1 – Montanide ISA 720 malaria vaccine) with 10 subjects in each cohort and
- 15 subjects will receive the control vaccine (i.e. Hepatitis B vaccine) with five (5) subjects in each cohort.

Subjects who are discontinued from the study following enrolment and after the first (1st) vaccination (drop-outs) will not be subsequently replaced.

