## 11.4 Assessment Endpoints

In Section 8 of this protocol, all clinical and biological endpoints are defined for evaluation of reactogenicity, safety, immunogenicity, at defined visits after the vaccination (assessments during the vaccination period and during the follow-up period). A detailed description of these variables will be provided in the SAP.

*Information contained in this publication is the property of EVI and ICGEB and is confidential and will not be disclosed to third parties without written authorization from EVI and ICGEB. No part of this document may be reproduced, stored in a retrieval system or transmitted in any form or by any means -electronic, mechanical, recording or otherwise - without the prior authorization of EVI and ICGEB*

[figure not shown][figure not shown]

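### In the documents shown, the differential white count has only percentage ranges, so its out-of-range flags can rank subjects in the wrong order on absolute count

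*Supplement*

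**What the plan says.** Section 4.6.1 of the protocol makes haematology part of the primary safety endpoint, judged against the baseline before the first dose. The list includes "Platelet Count and Total Leukocyte Count (TLC) along with Differential Leukocyte Count (DLC) on Days -14, 28, 56, 180, 208, 365".

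Section 11.5.1.3 sets the presentation: "Clinical laboratory results will be tabulated by vaccine group at each time point as both quantitative parameters (raw values) and qualitative parameters". The second form is worded as "qualitative parameters (relative positions regarding normal ranges in use in the laboratory". The section specifies change from pre-vaccination for vital signs. It does not specify change from baseline for laboratory values.

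Appendix B supplies reference ranges. The white cell count is 4.50 to 11.00 ×10³/µl. Neutrophils (40 to 75), lymphocytes (20 to 45), monocytes (2 to 10), eosinophils (1 to 6) and basophils (0 to 1) are all in percent. Eligibility also uses percentages: Section 5.4.2 has "Neutrophils 40 to 75 % or Eosinophils > 10" percent, and Appendix B-1 follows suit. No absolute differential count appears as a measured or derived variable.

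Two provisions qualify this. Section 11.5.1.3 adds that "Newly occurring or worsening lab abnormalities will be assessed and reported by the investigator as adverse events as applicable". Section 11.4 says of the endpoint variables: "A detailed description of these variables will be provided in the SAP". That SAP is not among the documents shown.

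**The concern.** A percentage of white cells describes composition, not how many cells of a type there are. The five percentages are tied together by their sum, so a rise in one cell type can push another's percentage out of range although its own count has not moved. The same percentage also stands for very different counts at different TLC values. A table counting subjects low or high on a percentage row can therefore flag the subject with more cells and pass the one with fewer.

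What is at stake is the readability of one part of the primary safety tables. Arms are small: one subject is 10 percentage points in a test arm of 10 and 20 points in a cohort's control arm of 5. That is true of any yes/no item in this trial, but it leaves little room for flags that do not track the cell count.

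**Working it through.** The plan states no figure to reproduce here; Section 11.1.1 says "true sample size calculations have not been performed and the sample size is approximately 45 healthy male subjects". The check is arithmetic on the Appendix B limits.

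**Formula.** Absolute count = TLC × percentage / 100, in ×10³/µl.

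**1. Span with no flag on either row (TLC 4.50 to 11.00, neutrophils 40 to 75%).**
- Upper: 11.0 × 0.75 = 8.25
- Lower: 4.5 × 0.40 = 1.80
- Largest unflagged fall: 1 − 1.80/8.25 = 78%

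Both corners are possible with the other rows in range: 40 + 45 + 10 + 5 + 0 = 100 and 75 + 20 + 3 + 2 + 0 = 100 (neutrophils, lymphocytes, monocytes, eosinophils, basophils). Away from the corners, 10.0 × 0.70 = 7.00 falling to 4.5 × 0.42 = 1.89 is an unflagged fall of 73%.

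**2. Wrong order.**

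| Cell type | Flagged | Not flagged |
|---|---|---|
| Neutrophils | 11.0 × 39% = 4.29 (low) | 4.5 × 40% = 1.80 |
| Lymphocytes | 11.0 × 19% = 2.09 (low) | 4.5 × 20% = 0.90 |
| Eosinophils | 4.5 × 7% = 0.315 (high) | 11.0 × 6% = 0.66 |

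For neutrophils the flagged count is 4.29/1.80 = 2.4 times the unflagged one. At 39%, any in-range TLC above 1.80/0.39 = 4.62 gives a low flag at a count above 1.80.

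**3. A flag with no change in the flagged cell type (hypothetical counts).** Start with neutrophils 4.0, lymphocytes 2.0, monocytes 0.40, eosinophils 0.20, basophils 0.05. TLC is 6.65 and every row is in range. Let only neutrophils rise, to 7.5. TLC is 10.15 and neutrophils are 7.5/10.15 = 73.9%, both in range. Lymphocytes are 2.0/10.15 = 19.7%, now flagged low with the lymphocyte count unchanged.

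**4. How far the unflagged region extends.** If neutrophils are at least 40%, a count below 1.80 requires TLC below 1.80/0.40 = 4.5, which is flagged on the TLC row. For example, 3.0 × 0.40 = 1.20 leaves the neutrophil row normal but TLC low. If neutrophils are below 40%, their own row is flagged. So no count below 1.80 escapes both rows.

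**5. Timing.** Section 8.2 bases escalation on safety data through Day 14 after the first dose. The first scheduled haematology after the first dose is Day 28 (Table 1).

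**The case against.** The strongest reply has four parts.

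- **The SAP may settle it.** Section 11 calls itself an outline, and derived laboratory variables are ordinary SAP content. That stands as a limit on what can be claimed: the SAP could add absolute counts. But the protocol already gives a classification rule and a set of percentage ranges, and the proposal is a better variable under that rule.
- **Appendix B may not be the set applied.** Section 11.5.1.3 refers to the laboratory's normal ranges without citing Appendix B, and the text cites that appendix for eligibility. So it is an inference that only percentages will be used. Appendix B is, however, the trial's table of laboratory reference ranges, and no other set is shown.
- **The 78% fall is not in itself a misclassification.** A reader might infer that absolute ranges would catch it. That does not follow: any normal range, absolute ones included, leaves a fall from its upper to its lower limit unflagged, and the documents give no absolute limits. This stands fully. Change from baseline is what shows such a fall; the case for absolute classification rests on the wrong order in step 2 and the induced flag in step 3.
- **Other safeguards exist.** Raw values are tabulated, so in the 78% example TLC drops from 11.0 to 4.5 (59%) in plain view. The endpoint is framed against baseline, and investigators review abnormalities as possible adverse events. These are real safeguards, though no numeric threshold is given for that review. They do not mend the flags, and group summaries of TLC and of percentages cannot be multiplied back to each subject's count.

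**Conclusion.** The point holds as a weakness in how the differential count is classified. On the Appendix B limits, neutrophils of 4.29 are flagged low while 1.80 is not, the same reversal occurs for lymphocytes and eosinophils, and a change in one cell type can flag another. With TLC and neutrophil percentage both in range, absolute neutrophils can lie anywhere from 8.25 to 1.80 ×10³/µl without a flag.

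This assumes that the Appendix B ranges are those used for the tables and that the unseen SAP does not add absolute counts. The documents give no basis for saying how often such cases would arise; the figures show what the rule permits.

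Two stronger readings are tempting and are not supported. One is that a dangerous neutropenia would go unseen: the TLC row bounds the unflagged region at 1.80, and raw values and investigator review remain. The other is that escalation is compromised: the DSMB review uses data through Day 14, before the first post-dose haematology, and no stated decision rule uses the out-of-range rates. The analysis is descriptive throughout. This is a worthwhile, low-cost improvement.

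**What to change.** In Section 11.5.1.3, or in the SAP:

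- Derive an absolute count for each differential cell type, per subject and scheduled visit, as TLC × percentage / 100.
- Summarise these counts by vaccine group and visit, with change from the screening baseline. This is the element that shows large falls within range.
- Classify the absolute counts against the central laboratory's own absolute ranges where it has them, and state which set of ranges is used. No cut-off is proposed here.
- Keep the percentage tables as supportive.

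TLC and the differential are already collected at screening and on Days 28, 56, 180, 208 and 365, so no extra blood or visits are needed. The cost is a few derived tables and a request to the laboratory for its absolute ranges.
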